## Abstract

This is a multicentre prospective randomised controlled trial for patients with 3 or more resectable pulmonary metastases from colorectal carcinoma. The study investigates the effects of pulmonary metastasectomy in addition to standard medical treatment in comparison to standard medical treatment plus possible local ablative measures such as SBRT. This trial is intended to demonstrate an overall survival difference in the group undergoing pulmonary metastasectomy. Further secondary and exploratory endpoints include quality of life (EORTC QLQ-C30, QLQ-CR29 and QLQ-LC29 questionnaires), progression-free survival and impact of mutational status. Due to the heterogeneity and complexity of the disease and treatment trajectories in metastasised colorectal cancer, well powered trials have been very challenging to design and execute. The goal of this study is to create a setting which allows treatment as close to the real life conditions as possible but under well standardised conditions. Based on previous trials, in which patient recruitment in the given setting hindered successful study completion, we decided to (1) restrict inclusion to patients with 3 or more metastases (since in case of lesser, surgery will probably be the preferred option) and (2) allow for real world standard of care (SOC) treatment options before and after randomisation including watchful waiting (as opposed to a predefined treatment protocol) and (3) possibility that patient can receive SOC externally (to reduce patient burden). Moreover, we chose to stipulate 12 weeks of systemic treatment prior to possible resection to further standardize treatment response and disease course over a certain period of time. Hence, included patients will be in the disease state of oligopersistence rather than primary oligometastatic. The trial was registered in the German Clinical Trials Register (DRKS-No.: DRKS00024727).

## Introduction

Pulmonary metastasectomy (PM) is a widely applied treatment for metastasised colorectal cancer (mCRC) based on findings from a vast abundance of retrospective trials (1–5). The only prospective trial on pulmonary mCRC has not shown any survival benefit for patients undergoing PM compared to systemic therapy only (6). Although the trial failed to reach its recruitment target and was thus underpowered the observed survival of 47% after 4 years in the control group is far better than expected and crucial when assuming a potential benefit from PM (7). Other prospective randomised trials have demonstrated a benefit for progression-free as well as overall survival by radical local ablative treatments in metastasised solid cancers including lung, breast, colorectal cancer (CRC) and others (8–11). Local ablative measures in these trials were either exclusively or mostly non-surgical consisting of stereotactic body radiation therapy (SBRT) and radiofrequency ablation. Moreover, the only trial exclusively including patients with hepatic metastases from CRC suffered, although randomised, from serious imbalances regarding number of metastases in the investigated groups (8).

Generally, the application of local ablative measures in metastasised cancers remains controversial. Some argue that systemic diseases should be treated as such and hence therapy should be confined to systemic treatment alone (12). Others believe that radical local measures result in survival advantages due to cytoreduction and removal of sites which are insufficiently treated by the medical treatment. Also, these sites could be capable of seeding new metastases. The significance of tumour cell release by secondary tumours for further metastasisation remains unclear, however, there is clinical and experimental evidence showing a beneficial effect of aggressive local ablative treatment in oligometastasis on further metastasisation (13–19)

Current guidelines of the European Society of Medical Oncology (ESMO) recommend resection of pulmonary metastases in cases in which R0-resection is feasible, however under consideration of relative contraindications based on the tumour biology as well as patient-related factors such as comorbidities and personal expectations (20).

The factors currently defining tumor biology include presence of a higher number of metastases, meta- vs. synchronicity of metastasisation and a short interval from diagnosis of the primary to first manifestation of metastasis [disease-free-interval (DFI)]. Due to the lack of strong evidence the interpretation of these relative contraindications is highly variable and the chosen treatment modalities depend largely on the treating institution and discipline. A benefit from surgical resection has never been proven in prospective trials even in patients with small numbers of metastases (1-3). Nevertheless, surgery in these patients is generally applied and considered treatment of choice in many countries. This is based primarily on retrospective data which shows a favourable prognosis in patients with completely resectable metastases, even if there are more than 3 lesions (2, 5). If surgical resection in comparison to the current standard of care proves superior in the study presented here, PM could be implicated as standard of care option also in patients with multiple metastases and thus help to improve long-term survival of these patients; on the other hand, a negative finding could result in abandoning the practice of PM at least in a selected cohort.

To our knowledge there is currently only one ongoing other multi-centric prospective randomised controlled trial on PM conducted by the MD Anderson Cancer Center in Texas, USA which started recruitment in July 2018 (NCT03599752). Patients are categorised into low and high risk before being randomised. Low risk patients are randomised to either PM + systemic treatment or PM alone. High-risk patients are randomised to either PM + systemic treatment or systemic treatment alone. Primary outcome measures are progression-free survival (PFS) in the low-risk group and overall survival (OS) in the high-risk group.

Although past prospective randomised trials either failed to reach the targeted recruitment numbers and/or suffered from patient heterogeneity we hope that further, carefully designed prospective trials, as the one we present here, can provide additional insight into the potential benefits of surgical removal of pulmonary metastases in patients with CRC.

## Methods and Analysis

### Design

This is a multicentre prospective randomised controlled trial for patients with 3 or more resectable pulmonary metastases from CRC. PUCC investigates the effects of pulmonary metastasectomy in addition to standard medical treatment in comparison to standard of care, i.e. medical treatment and/or alternative local ablative measures such as stereotactic body radiation therapy (SBRT).

This trial is intended to demonstrate an overall survival benefit in the group undergoing pulmonary metastasectomy. For the trial start a total of about 15 sites have agreed to participate in this multicentre trial. Then, if necessary more sites will be included and in case of recruitment failure, the respective sites will be replaced. The planned recruiting period is 2 years.

### Endpoints

The primary endpoint is overall survival (OS). OS is defined as the time from randomisation until death from any cause with censoring at the last date alive. The primary objective is to assess the effect of pulmonary metastasectomy compared to standard of care consisting of systemic therapy and possible SBRT where indicated on OS.

Secondary endpoints are

Progression-free survival (PFS), defined as the time from randomisation until disease progression or death from any cause.PFS assessment will be performed locally, usually in a multidisciplinary setting (e.g. tumour board) but at least by a radiologist and oncologist/thoracic surgeon.Definitions of progressive disease (PD) can consist of but are not limited to: unequivocal tumour growth of known metastatic lesions, new metastatic lesions, local recurrence.PFS will be determined from serial CT scans, PET-CT or MRT with censoring at the last date alive and progression-free.Complete remission, defined as no radiologic sign of residual disease and pathologically complete (R0) resection if applicable.Quality of life (QoL) using the EORTC QLQ-C30, QLQ-CR29 and QLQ-LC29 questionnaires at 3, 6, 12, 24 and 36 months after randomisation.

### Participants

Patients with at least 3 technically resectable (R0) pulmonary metastases from colorectal cancer will be enrolled into this trial. A total of 152 patients are planned to be randomised at a 1:1 ratio (about half of the patients to each treatment arm).

#### Main Inclusion Criteria

Histologically confirmed colorectal adenocarcinoma≥ 3 technically resectable (R0) pulmonary metastasesMale or female patients aged ≥ 18 years without upper age limitResected primary tumour with intent to cure (sole prior (chemo) radiation of a rectal cancer with documented complete remission is permitted)In case of previous treatment of hepatic metastases: no radiologic sign of active hepatic disease at the time of trial randomisationA minimum of 12 weeks of systemic therapy with the last treatment applied within 6 months prior to randomisationGood performance status (ECOG 0-1)Sufficient pulmonary reserve (FEV1 >60%, DLCO >60%)

#### Main Exclusion Criteria

Active extra-thoracic tumour disease (including primary tumour *in situ*)Prior resection of lung metastases (diagnostic resection is allowed)Requirement of a pneumonectomy to achieve complete resectionOther malignancy in the past 5 years (except non-melanoma skin cancer or *in situ* cancer)Histologically proven intrathoracic lymph node metastasis (except resectable single level mediastinal, hilar and pulmonary) as defined at https://radiopaedia.org/articles/thoracic-lymph-node-stations
Known or uncontrolled brain metastasesKnown BRAF V600E mutation (unknown BRAF mutation status does not constitute an exclusion criterion)Prior >2^nd^ line therapy, i.e. TAS-102 (Lonsurf^®^) or regorafenib

9. Medical condition which poses a high risk to undergo systemic treatment and/or surgery as defined by the investigator

### Treatment

All trial participants must have received at least 12 weeks of standard systemic treatment, with the last treatment applied within 6 months prior to randomisation. Chemotherapy can have been carried out at the discretion of the treating oncologist and according to local standards/guideline recommendations and must have consisted of a cytotoxic therapy (monotherapy, doublet or triplet) with or without a VEGF-or EGFR-directed therapy.

If the patients are randomised to Arm A, the pulmonary metastasectomy surgery should be performed as soon as possible after completion of systemic therapy (as defined in inclusion criterion 6) but no sooner than 4 weeks after last application of systemic therapy.

Before trial enrolment, all patients will require restaging *via* PET-CT or CT-thorax and -abdomen or CT-thorax plus MRI abdomen within 6 weeks before randomisation. If a patient has 3 or more isolated lung metastases, the patient will be assessed for trial inclusion by an experienced thoracic surgeon, preferably in the setting of a multidisciplinary tumour board. If the metastases are amenable to surgical resection and the inclusion criteria are met, then the patient will be randomised (**Figure 1**).

**Figure 1 f1:**
[figure not shown]
* For Arm B this includes the possibility of local ablative measures such as SBRT. # For Arm A (Surgery) this includes the possibility of re-resection.

#### Experimental Treatment (Arm A)

After randomisation into the experimental treatment arm patients will undergo uni- or bilateral surgical resection of the pulmonary metastases.

In case of bilateral disease patients will undergo one side first and after 3-5 weeks the other side. A CT scan of the thorax should be performed after the first surgery and before the second. Remaining metastases after resection on the ipsilateral side do not result in trial exclusion or pose a contraindication to resection of the remaining side. If the lesions are amenable to safe and complete resection, lesions can be removed by the means of minimally invasive surgery. Also, according to surgeon’s preference single-stage bilateral resection *via* sternotomy can be carried out. Single stage bilateral thoracotomy is not recommended. Anatomical resection (segmentectomy, lobectomy) can be applied if it is required to provide safe R0-resection.

Any currently available standard-device can be used for resection according to local standards. If cautery or laser-devices are used the resulting defects should be sutured with a monofilament absorbable suture (e.g. PDS™).

In case of diffuse metastasisation and or pleural carcinosis the surgery must be aborted. Systematic lymphadenectomy or sampling is recommended in patients in Arm A. If mediastinal lymph node metastases are ruled out by PET-CT and/or endobronchial ultrasound guided biopsy (EBUS), lymphadenectomy can be omitted.

After completion of surgical treatment in Arm A the patients will continue with systemic treatment according to the standard of care. Postoperative continuation of systemic therapy will be decided upon investigator’s discretion. If adjuvant treatment is chosen, then this should preferably consist of fluorouracil (alternatively capecitabine) and oxaliplatin. Given the lack of benefit of regimens containing irinotecan, EGFR-targeted agents and VEGF-targeted agents in the adjuvant treatment of stage II or III colon cancer, these should only be used on an individual basis in the postoperative setting.

In the experimental arm, it is encouraged that patients undergo re-resection in case of disease progression/recurrence if the respective oncologic principles apply.

#### Control Treatment (Arm B)

After randomisation into the control arm patients will continue standard of care consisting of systemic therapy. Standard of care should follow common oncologic recommendations. SBRT can be applied upon investigator’s discretion.

Data on the standard anti-tumour care (chemotherapy and SBRT) will be collected and analysed **Figure 2**.

**Figure 2 f2:**
[figure not shown]
EOS, End of Study; FU, Follow-Up; MH, Medical history; Mo, month(s); pt(s), patient(s); Rando, randomisation; SBRT, Stereotactic Radiation Therapy; W, week(s). (1) Investigations during the treatment period are performed at the discretion of the treating physician and according to the respective treatment arm. (2) Randomisation has to be performed as close as possible to potential start of surgery. (3) Quality of life (QoL) will be assessed using the EORTC QLQ-C30, QLQ-CR29 and QLQ-LC29 questionnaires. (4) Laboratory includes LDH, CEA, CA19-9, CRP (see section 7.8.8 Blood tests). (5) Not older than 6 weeks at the time of randomisation. (6) Number of nights in hospital will be documented starting from the randomisation date and until the end of the month 12. (7) Might be assessed externally, if not possible at trial site due to Covid19.

### Informed Consent Procedure

Before enrolment in the clinical trial, the patient will be informed that participation in the clinical trial is voluntary and that he/she may withdraw from the clinical trial at any time without having to give reasons and without penalty or loss of benefits to which the patient is otherwise entitled. The treating physician will provide the patient with information about the treatment methods to be compared and the possible risks involved. At the same time, the nature, significance, implications, expected benefits and potential risks of the clinical trial and alternative treatment will be explained to the patient. The patient’s written consent must be obtained before any trial-specific tests/treatments. For this purpose, the written consent form will be personally dated and signed by the trial patient and the investigator conducting the informed consent discussion.

### Randomisation Methodology

Randomisation will be performed, stratified by site, in blocks of variable length aiming for large block lengths in a ratio of 1:1 to ensure a balanced distribution of the treatments and reduce selection bias. The block lengths will be documented separately and will not be disclosed to the sites. Central randomisation will be performed web based using the RedCap™ tool to conceal treatment allocation.

### Data Management and Monitoring

The data management will be performed with REDCap™, a fully web based remote data entry (RDE) system (also called eCRF). The system is based on web forms and is developed and maintained by the REDCap Consortium ([contact]). The technical specifications of the database will be described in the codebook delivered automatically by the REDCap™ system.

Details on data management (software, procedures, responsibilities, etc.) will be described in a data management plan prior to the trial. During the trial, the performance of data management and any deviations from the data management plan will be documented in a data management plan. Technical specifications of the trial data base and all data checks will be documented in a data validation plan.

The trial data base has been fully validated before any data entry will be performed. Data entry personnel will not be given access to the trial data base until they have been trained. The investigator or a designated person will record the participation in the trial, the frequency of the trial visits, the relevant medical data, the concomitant treatment and the occurrence of adverse events in the medical record of each trial patient, as timely as possible. An audit trail provide a data history which data were entered, changed or deleted, by whom and when.

Data will be checked during data entry by so-called built-in edit checks. The data will be further reviewed for completeness, consistency, plausibility, and regarding protocol violations and other distinctive problems (e.g. cumulative missings) using SAS software. The resulting queries will be sent to the investigator for correction or verification of the documented data. All programs which can be used to influence the data or data quality will be validated (e.g. edit check and data validation programs for import of external data, etc.).

Concomitant treatments or procedures entered into the eCRF will be coded using the WHO Drug Reference List. Adverse Events will be coded using the Medical dictionary for regulatory activities (MedDRA) terminology.

Information about trial patients will be kept confidential and managed under the applicable laws and regulations. Those regulations require a signed patient authorisation informing the patient of the following:

· what protected health information (PHI) will be collected from patients in this trial;· who will have access to that information and why;· who will use or disclose that information;· the rights of a research patient to revoke their authorisation for use of their PHI.

In the event that a patient revokes authorisation to collect or use PHI, the investigator, by regulation, retains the ability to use all information collected prior to the revocation of patient authorisation. For patients that have revoked authorisation to collect or use PHI, attempts should be made to obtain permission to collect at least vital status (i.e. that the patient is alive) at the end of their scheduled trial phase. The data collection system for this trial uses built-in security features to prevent unauthorised access to confidential participant information, including an encrypted transport protocol for data transmission from the participating sites to the trial database. The trial database is located on a server of the IT facility of Medical Center - University of Freiburg. Employees of the Clinical Trials Unit charged with hosting the eCRF and the trial database are obliged to maintain data confidentiality and to comply with data protection regulation.

### Biostatistical Planning and Analysis

The sample size calculation is based on the primary endpoint overall survival. A median OS time of approximately 27 months under standard of care is assumed, while the median OS time is expected to increase to about 55 months under standard of care (without SBRT) and pulmonary metastasectomy (2, 21). This corresponds to a hazard ratio of 2.04 between the treatment arms (medical treatment vs. medical treatment and pulmonary metastasectomy). The effect of medical treatment and pulmonary metastasectomy will be assessed by a log-rank test at two-sided significance level of 5% and by estimation of the hazard ratio with corresponding asymptotic two-sided 95% confidence interval. The null hypothesis is rejected, if the confidence interval does not contain one. Under the above assumptions, the trial is planned to detect a difference between medical treatment and pulmonary metastasectomy over medical treatment alone with a power of 90%, which requires a total number of 83 events to be observed. To account for the possibility that the observed hazard ratio may be diminished by non-compliance and/or drop-out of patients, the sample size is calculated to achieve a power of 90%. The required number of patients to be randomised to observe this amount of events depends on the length of follow-up. With a recruitment period of 2 years, an additional follow-up period after the end of recruitment of 3 years (maximum length of follow up 5 years) it can safely be assumed that a sufficient number of events will have been observed by the end of the trial if a total of 152 patients (76 per group) are available for analysis (software used, e.g. nQuery Advisor 8.3).

### Definition of Populations Included in the Analyses

Efficacy analyses will be performed primarily in the full analysis set (FAS) according to the intention-to-treat (ITT) principle. This means that the patients will be analysed in the treatment arms to which they were randomised, irrespective of whether they refused or discontinued the treatment or whether other protocol violations occurred.

The per-protocol (PP) population is a subset of the FAS and is defined as the group of patients who had no major protocol violations, received a predefined minimum dose of the treatment and underwent the examinations required for the assessment of the endpoints at relevant, predefined times. The analysis of the PP population will be performed for the purpose of a sensitivity analysis. Safety analyses will be performed in the safety population. Patients in the safety population are analysed as belonging to the treatment arm defined by treatment received. Patients are included in the respective treatment arm, if treatment was started/if they received at least one dose of trial treatment.

### Primary Endpoint

The effects of standard of care with and without metastasectomy with respect to the primary endpoint overall survival will be estimated and tested by Cox regression. The regression model will include treatment and trial site as independent variables, as well as, metachronicity vs. synchronicity and, previous treatment of hepatic metastasis and colon- or rectal cancer. As estimate of the effect size, the hazard ratio between the two treatment arms will be given with the corresponding asymptotic two-sided 95% confidence interval. The two-sided test on difference between standard of care with metastasectomy and standard of care at significance level 5% will be based on the corresponding asymptotic two-sided 95% confidence interval from the Cox regression model. Overall survival will be analysed irrespective of the occurrence of intercurrent events. This is consistent with the treatment policy strategy of the estimands framework.

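### Number of metastases, which the article treats as prognostic and for whose imbalance it faults another trial, is neither a stratification factor nor a covariate in the primary Cox model

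*Protocol article*

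**What the plan says.** All references are to the protocol article.

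- **Introduction, on prior evidence.** A cited randomised trial in hepatic metastases "suffered, although randomised, from serious imbalances regarding number of metastases in the investigated groups".
- **Introduction, on prognosis.** "The factors currently defining tumor biology include presence of a higher number of metastases"; synchronous versus metachronous spread and a short disease-free interval follow as separate items. The Discussion again lists number of metastases and disease-free interval as conventional risk parameters, and partly blames imbalance between groups for the ambiguous results of past trials.
- **Randomisation Methodology.** "Randomisation will be performed, stratified by site, in blocks of variable length". No other stratification factor is named.
- **Primary Endpoint.** The Cox model contains treatment and trial site, "as well as, metachronicity vs. synchronicity and, previous treatment of hepatic metastasis and colon- or rectal cancer". The Secondary Endpoints section carries the same approach over to progression-free survival.
- **Participants and Treatment.** Patients need at least three resectable pulmonary metastases, with restaging no more than 6 weeks before randomisation and assessment by a thoracic surgeon.

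**The concern.** The article identifies a prognostic factor, shows by example what an imbalance in it can do to a randomised trial, and then describes a design and a primary analysis that do nothing about it. This is not detail left to an analysis plan: the Primary Endpoint section states the covariate list, and number is not on it.

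Two things are at stake. First, if the arms happen to differ in number of metastases, the hazard ratio shifts with that difference and the planned model cannot correct it. An adjustment added after the data are seen would look chosen for its result, and leaving it out would invite the criticism that the article makes of the earlier trial. Second, omitting a prognostic covariate from a Cox model pulls the treatment estimate towards 1 and costs some power.

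**Working it through.** **Inputs from the article.** 152 patients, 76 per arm; medians of 27 and 55 months; a "log-rank test at two-sided significance level of 5" per cent; 2 years of recruitment plus 3 years of follow-up; about 15 sites.

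**Assumption.** The article gives no prognostic strength for number of metastases. A hazard ratio of 1.2 to 1.7 per SD of log number is assumed.

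**1. The plan's own figure.** The article claims to detect the difference "with a power of 90%, which requires a total number of 83 events to be observed". Schoenfeld's formula gives 4 × (1.960 + 1.282)² / (ln 2.04)² = 42.03 / 0.508 = 82.7, so 83 events. This is reproduced. With exponential survival and uniform accrual, the probabilities of death by study end are 0.704 and 0.452, so 76 × (0.704 + 0.452) ≈ 87.8 deaths are expected against 83 required. The calculation is a log-rank one and takes no credit for covariates.

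**2. Chance imbalance.** The SD of the difference in standardised means is √(2/76) = 0.162.

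| Imbalance of at least | z | Two-sided probability |
|---|---|---|
| 0.25 SD | 1.54 | 12% |
| 0.40 SD | 2.47 | 1.4% |
| 0.50 SD | 3.08 | 0.2% |

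For a yes/no factor at 50% prevalence, the SD of the difference is √(2 × 0.25/76) = 0.081. A gap of at least 10 percentage points then has probability 22%, 15 points 6%, and 20 points 1.4%.

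**3. Effect of an imbalance on the hazard ratio.** To a first approximation the log hazard ratio shifts by imbalance × ln(HR per SD). For 0.25 SD:

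- HR 1.2 per SD: 0.25 × 0.182 = 0.046, about 5%.
- HR 1.5 per SD: 0.25 × 0.405 = 0.101, about 11%. Simulation of an unadjusted Cox model gave a slope of 0.44, hence 0.25 × 0.44 = 0.11, about 12%.
- HR 1.7 per SD: 0.25 × 0.531 = 0.133, about 14%.

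At the design value of 27/55 = 0.49, a 12% shift would read as about 0.55 (0.49 × 1.12) or 0.44 (0.49 / 1.12).

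**4. Power, against the model actually planned.** Simulated trials of 152 patients with 15 fixed site effects and the three planned covariates, 1,500 runs per setting (simulation error about 1 point), fitted with and without number:

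| Assumed HR per SD | Power lost by omitting number |
|---|---|
| 1.2 to 1.3 | about 0 to 1 point |
| 1.5 | about 2.5 points |
| 1.7 | about 5 points |

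A separate simulation used 3,000 runs, no site terms, and a high-number category in half of the patients. Adding number to a model with treatment and synchronicity changed power from 0.899 to 0.907 (HR 1.5 for high number), 0.882 to 0.910 (HR 2.0) and 0.855 to 0.901 (HR 2.5). The scale is the same.

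**5. Disease-free interval.** In that second simulation, synchronous disease was taken as the shortest 40% of intervals, with an effect of 1.25 to 1.5 per SD. Adding the continuous interval on top of synchronicity and number changed power from 0.896 to 0.900, 0.900 to 0.902 and 0.882 to 0.893 in the three settings with high-number HR 2.0 or 2.5, a gain of about 0 to 1 point.

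**6. Type I error.** With no treatment effect, the model without number rejected in 5.1% of runs, so omission does not inflate the error rate.

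**The case against.** **Number may not be strongly prognostic here.** The Introduction itself speaks of a lack of strong evidence for these relative contraindications and reports favourable outcomes after complete resection even with more than three lesions. Eligibility also narrows the range: although no maximum appears among the main criteria, every lesion must be technically resectable without pneumonectomy, in patients with adequate lung function. This stands. The prognostic strength is an assumption, and at its weak end almost no power is lost.

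**A reader might infer that the 90% power is wrong.** The documents do not support that. The power comes from an unadjusted log-rank calculation that reproduces, and about 88 deaths are expected against 83 needed. Power is lost only relative to a richer model.

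**A reader might infer that disease-free interval is missing in the same way.** It is not. Synchronous versus metachronous status is a coarse split of that interval and is in the model. Only its gradation is absent, and that is worth little.

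**A reader might expect the serious imbalance of the cited trial to recur.** It can, but large imbalances are improbable: 1.4% for 0.4 SD or more. The 12% refers to a moderate imbalance, which may favour either arm.

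**The model is already large.** Treatment, 14 site terms and three covariates make about 18 parameters, or 83/18 ≈ 4.6 events per parameter. This is a fair reason to add as little as possible.

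None of this explains why a factor that the article singles out is left off a stated covariate list.

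**Conclusion.** The point holds as one of efficiency and protection against chance imbalance. Number of metastases is absent from both the stratification and the primary model, against the article's own reasoning. There is about a 12% chance of an imbalance of at least 0.25 SD, which would move the treatment hazard ratio by roughly 12% if one SD of log number carries a hazard ratio of 1.5 (about 5% to 14% over the assumed range of 1.2 to 1.7). Omission costs about 0 to 5 power points over that range. The probability follows from the arm size alone; the shift and the power loss rest on the assumed prognostic strength.

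The trial remains valid without the change. The stated event number and power stand, type I error is not affected, and disease-free interval is already partly covered.

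**What to change.** Add the baseline number of pulmonary metastases, as log count (one degree of freedom), to the pre-specified covariates of the primary Cox model and of the progression-free survival model. Define it as the count on the eligibility restaging, before randomisation, for both arms. A count taken at surgery would exist only in Arm A.

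Graded disease-free interval is optional. If it is added alongside synchronicity, its coding for synchronous patients must be stated. No further stratification is needed: with about 15 sites averaging about 10 patients (152/15), another factor would leave many incomplete blocks.

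The cost is a change of wording before outcome data are seen, a data field if the count is not already recorded, and one more parameter: about 19 instead of 18, or 83/19 ≈ 4.4 events per parameter instead of 4.6.
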